#### Recruitment {15}

Both participating clinical centres perform more than 1 000 spinal surgeries per year. Among these, more than 80 patients with single-level lumbar stenosis met the inclusion criteria for the study. We expect that up to 40% of patients provide their informed consent to participate in randomization. Consequently, we suggest to reach the required sample size within 2 years.

## Assignment of interventions: allocation

### Sequence generation {16a}

All participants who meet the inclusion criteria and provide informed consent will be randomly divided into two equal groups (1: 1) according to the applied surgical technique. For the block randomization procedure, stratification based on the severity of lumbar stenosis (Schizas C and D) will be performed. Randomization will be by random permuted blocks of 4 and 6.

### Concealment mechanism {16b}

Participant allocation will be conducted using sequentially numbered, opaque and sealed envelopes, opened only at the time of participant’s inclusion in the study.

### Implementation {16c}

Randomization will be provided one day preoperatively by an independent remote study team member excluded from any other study roles. Randomization parameters will be documented in the participants’ records.

## Assignment of interventions: blinding

### Who will be blinded {17a}

Not applicable, no blinding.

### Procedure for unblinding if needed {17b}

The design of the study is open label with only outcome assessors being blinded, so unblinding will not occur.

## Data collection and management

### Plans for assessment and collection of outcomes {18a}

The study coordinators in all involved clinical centres are responsible for data collection and administration at baseline and during follow-up. All examinations (questionnaires, scales, radiography, and CT) will be performed during personal follow-up visits at the original centre of surgery performance.

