### Eligibility criteria {10}

Primary patient selection will be performed before admission. The study will include participants aged 45–75 years with symptomatic single-level stenosis at the level of L2-L3, L3-L4, L4-L5, or L5-S1 vertebrae. The inclusion and exclusion criteria are presented in Table 1. Patients who meet the inclusion criteria but refuse to participate in the study will be marked with an appropriate explanation.

**Table 1 Tab1:** Inclusion and exclusion criteria

Inclusion criteria:
- Age ranging from 45 to 75 years
- C or D grade lumbar stenosis at the level of L2-L3, L3-L4, L4-L5, or L5-S1 vertebrae (classification by Shizas et al.) according to MRI evaluation
- A clinical manifestation of lumbar stenosis (neurogenic claudication syndrome and/or radiculopathy)
- Insufficient conservative therapy within 3 months prior to surgery
- Informed consent was obtained from all included subjects
Exclusion criteria:
- Spondylolisthesis exceeding 3 mm
- Spinal instability according to functional radiography
- Sagittal imbalance (type 4 according to C. Barrey)
- Bone density of the vertebrae at the surgery level below 100 HU
- Clinically significant multi-level spinal stenosis (two or more segments)
- Previously performed surgeries at the lumbar level
- Severe sacroiliac or lumbar facet joint pain
- Risk of anaesthesia exceeding four or five grades according to ASA
- Inability to participate in control examinations within 2 years, postoperatively
- Participation in other clinical trials related to surgical or conservative treatment of spine diseases

A flow chart of the trial is provided in Fig. 1.

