## Outcomes {12}

### Primary endpoint

The primary endpoint includes the dynamics of ODI parameters at the end of the 24-month follow-up compared to the baseline level [7]. This patient-reported measurement precisely estimates the impairment of a participant’s quality of life resulting from low back pain and clearly reflects the clinical outcome of the treatment. Parameter assessment is to be considered at all stages of the study beginning from baseline examination, followed by a follow-up examination 2 years postoperatively. The questionnaire consists of 10 sections, comprising six statements per section. Each answer is assessed using six grades (ranging from 0 to 5) with a maximum score of 50 points per participant. Subsequently, the total score is converted into a percentage ratio (from 0 to 100%). If any of the sections are not applicable or have been withdrawn for ethical reasons, the total score is calculated within nine sections and is divided by 45.

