#### Sample size {14}

Following a non-inferiority study design, we calculated the sample size based on the primary outcome. According to the most recent randomized trial [6], the standard deviation for the ODI in the fusion group is 20 points. With a non-inferiority margin of δ = 12, two-sided α-level of 0.05, power of 80%, and 1:1 allocation ratio, the required sample size is 70 patients. Considering the potential of 20% of patients missing the obligatory follow-up procedures, we plan to include at least 86 patients (43 patients per group).

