### Plans to promote participant retention and complete follow-up {18b}

Communication with patients will be carried out via e-mail in accordance with the approved schedule (Table 2). If after 3 letters the patient does not get in touch, a phone call will be made. If the patient is not found within 2 weeks after the date of the follow-up visit, he will be excluded from the study.

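### The primary ODI is tied to a personal visit at the operating centre, so a patient who is in contact but does not attend at 24 months has an imputed outcome that could have been observed

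*Protocol article*

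**What the plan says.** The Protocol article gives the rule twice in the same words, under Participant timeline {13} and under Plans for assessment and collection of outcomes {18a}: "All examinations (questionnaires, scales, radiography, and CT) will be performed during personal follow-up visits at the original centre of surgery performance". Table 2 schedules the ODI before surgery and at 3, 6, 12 and 24 months.

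The Primary endpoint section defines the outcome: "The primary endpoint includes the dynamics of ODI parameters at the end of the 24-month follow-up compared to the baseline level". It describes the instrument as self-reported: "This patient-reported measurement precisely estimates the impairment of a participant’s quality of life resulting from low back pain".

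Plans to promote participant retention and complete follow-up {18b} sets up e-mail contact on the visit schedule and then a second channel: "If after 3 letters the patient does not get in touch, a phone call will be made". The same section deals with patients who cannot be located: "If the patient is not found within 2 weeks after the date of the follow-up visit, he will be excluded from the study". It does not deal with a patient who is located but does not attend.

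Three other provisions bear on the point. Table 1 excludes patients at entry for "Inability to participate in control examinations within 2 years, postoperatively". The Sample size {14} section enlarges the trial with the words "Considering the potential of 20% of patients missing the obligatory follow-up procedures". Section {20c} provides multiple imputation for missing outcomes.

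**The concern.** Radiographs, CT and MRI need attendance. A ten-section questionnaire filled in by the patient does not. Because one sentence covers both, a missed visit also loses the primary outcome, even when the patient is replying to e-mails or answering the telephone.

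Patients who are reachable but stay away at two years are unlikely to be a random subset. Some may be too disabled to travel, and others may be well enough to see no reason to come. In an open-label comparison the balance between the two could also differ by arm. Earlier ODIs can inform the imputation. If attendance at 24 months depends on disability at that time, however, they may not be enough, and the non-inferiority conclusion then leans on an imputation model where an observed value was within reach.

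**Working it through.** **Step 1: is there a route to an ODI without a visit?** Sections {13} and {18a} name questionnaires and scales in the personal-visit rule. Section {18b} uses e-mail and telephone for contact and tracing only. No section of the article describes postal, electronic or telephone completion. A patient who is reached but does not attend therefore has no stated way to give an ODI.

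**Step 2: the plan's own figures.** Inputs from Sample size {14}: SD 20, margin 12, power 80%, 1:1 allocation, 70 evaluable, 20% loss, 86 enrolled. The true difference is taken as 0.

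n per arm = 2 × SD² × (z_α + z_β)² / margin²
- One-sided 5%: 2 × 400 × (1.645 + 0.842)² / 144 = 34.4, so 35 per arm and 70 in total. This matches the stated 70.
- Two-sided 5%, as stated: 2 × 400 × (1.960 + 0.842)² / 144 = 43.6, so 44 per arm and 88 in total. This does not match. It is a separate matter and the present point does not depend on it, so both levels are shown below.
- Loss: 70 / 0.8 = 87.5, so 88, against the stated 86.

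**Step 3: how many outcomes are involved.** 20% of 86 is 17.2 missing, leaving 68.8 observed. The documents do not split the 20% into patients not found, patients withdrawn, and patients in contact but absent. Only the last group is recoverable by e-mail, post or telephone. As an illustration, assume a quarter to a half of the loss is of that kind: 17.2 × 0.25 = 4.3 and 17.2 × 0.5 = 8.6 additional observed ODIs.

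**Step 4: effect on complete-case power.** SE = 20 × √(2 / n per arm); power = Φ(12 / SE − z).

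| Share of loss recovered (assumed) | Observed ODIs | n per arm | SE | Power, one-sided 5% | Power, two-sided 5% |
|---|---|---|---|---|---|
| None | 68.8 | 34.4 | 4.82 | 80.1% | 70.1% |
| A quarter | 73.1 | 36.55 | 4.68 | 82.1% | 72.7% |
| A half | 77.4 | 38.7 | 4.55 | 84.0% | 75.2% |

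The gain is 2.0 to 2.6 points for a quarter and 3.9 to 5.1 points for a half. These are ceilings for each assumption. They compare complete cases, whereas the plan imputes, and ODIs at 3, 6 and 12 months may already recover part of the precision.

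**The case against.** The strongest reply is that completing questionnaires at a clinic visit is a legitimate choice and that the passages agree with one another. The sentence states the planned mode without expressly forbidding a fallback, and what happens after a missed visit might be set out in the full protocol. The article also has safeguards: exclusion at entry of patients who cannot attend for two years, reminders, a 20% allowance, and imputation supported by earlier ODIs.

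Part of this stands. Nothing is contradicted and no figure is wrong. But the rule is explicit and names questionnaires, so the point does not rest on silence alone. A criterion judged at entry cannot foresee later disability, relocation or unwillingness; the allowance accepts the loss; and imputation models the value without observing it.

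A reader might infer three stronger things that the documents do not support.
- **That the whole 20% is recoverable**, taking power to 87.2% or 79.4%. The allowance is not split by reason, and patients who are not found or who withdraw cannot be recovered this way. The recoverable share could be close to zero.
- **That the visit rule leaves the trial underpowered.** On the basis that reproduces 70, power at the full planned loss is already 80.1%. The 70.1% figure comes from the mismatch between the stated two-sided level and the sample size.
- **That a mode effect could be checked once mode is recorded.** Remote forms would come only from non-attenders, so mode is confounded with the reason for absence, and there would be only a handful of forms.

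It also stands that a telephone ODI brings in an interviewer who may know the allocation, and that long instruments such as the 64-question CPCI are poorly suited to the telephone. That argues for limiting the change to the ODI.

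**Conclusion.** The point holds as a modest, inexpensive improvement to data collection. Following the rule as written replaces an obtainable primary outcome with an imputed one for any patient who is in contact but absent at 24 months. Its size cannot be derived from the documents. On the assumption that a quarter to a half of the budgeted loss is of this kind, it amounts to about 4 to 9 observed ODIs and at most about 4 to 5 points of complete-case power, and less under the planned imputation. The more durable benefit is less dependence on the imputation model in a non-inferiority comparison.

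**What to change.** Amend the sentence in sections {13} and {18a}. Keep the personal visit as the default for all assessments and as the requirement for imaging and examination. When a visit is missed, allow the ODI to be self-completed by e-mail or post or, failing that, taken by telephone with a fixed script. Record the mode, count these forms as observed data, and add a sensitivity analysis that leaves them out.

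The cost is a revised sentence in two places, a mode field on the form, a short telephone script and one extra analysis. No visits or patients are added, and the contact channels exist. The downside is a possible mode effect in a few forms that cannot be separated from the reason for non-attendance. The sensitivity analysis shows whether the conclusion depends on those forms, but it does not estimate the mode effect.

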### Plans to promote participant retention and complete follow-up {18b}

Communication with patients will be carried out via e-mail in accordance with the approved schedule (Table 2). If after 3 letters the patient does not get in touch, a phone call will be made. If the patient is not found within 2 weeks after the date of the follow-up visit, he will be excluded from the study.

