**Methods:**

This study is focused on the non-inferior clinical results of decompression compared with the standard fusion procedure. In the decompression group, the spinous process, the interspinous and supraspinous ligaments, part of the facet joints, and corresponding parts of the vertebral arch are to be preserved intact. In the fusion group, decompression is to be supplemented with transforaminal interbody fusion. Participants meeting the inclusion criteria will be randomly divided into two equal groups (1:1), depending on the surgical method. The final analysis will include 86 patients (43 per group). The primary endpoint is Oswestry Disability Index dynamics at the end of the 24-month follow-up compared to the baseline level. Secondary outcomes included those estimated using the SF-36 scale, EQ-5D-5L, and psychological scales. Additional parameters will include sagittal balance of the spine, fusion results, total cost of surgery, and hospital stay followed by two-year treatment. Follow-up examinations will be performed at 3, 6, 12, and 24 months

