## Statistical methods

### Statistical methods for primary and secondary outcomes {20a}

The results will be analysed using the intention-to-treat principle. Statistical significance will be defined as *p* < 0.05 based on a two-sided test. No adjustments for multiple tests are planned. The normality of variables will be evaluated using the Shapiro-Wilk statistic. Student’s *t*-test (for normally distributed data) and Pearson’s chi-square test (for categorical data) will be used to reveal differences in symptom rates among the groups. Multiple linear regression will be used to measure point estimates and confidence intervals for group differences in the ODI and clinical scale scores from baseline to the 2-year follow-up.

The non-parametric Mann-Whitney *U* test will be used to reveal differences in continuous variables between groups both pre- and postoperatively. Continuous data within the groups will be compared using the Wilcoxon test. Categorical parameters among the groups will be compared using Fisher’s exact two-tailed test.

Complication incidence during the 2-year follow-up will be compared between groups using Kaplan–Meier survival curves and the log-rank test. The significance of the risk factors (predictors) for all registered complications will be evaluated using univariate and multivariate logistic regression models.

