### Methods in analysis to handle protocol non-adherence and any statistical methods to handle missing data {20c}

For missing outcome data, multiple imputations will be used.

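### The rule excluding patients not found within 2 weeks of a follow-up visit conflicts, read literally, with intention to treat and imputation, and on any reading leaves obtainable 24-month ODI values uncollected

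*Protocol article*

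**What the plan says.** Under *Plans to promote participant retention and complete follow-up {18b}*, patients are contacted by e-mail according to the visit schedule. "If after 3 letters the patient does not get in touch, a phone call will be made". Then: "If the patient is not found within 2 weeks after the date of the follow-up visit, he will be excluded from the study". The section does not say which visit is meant, and the abstract lists four: "Follow-up examinations will be performed at 3, 6, 12, and 24 months".

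Four other statements bear on this rule:

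- Analysis principle, *Statistical methods {20a}*: "The results will be analysed using the intention-to-treat principle".
- Missing data, section *{20c}*: "For missing outcome data, multiple imputations will be used".
- Primary outcome, *Primary endpoint*: "The primary endpoint includes the dynamics of ODI parameters at the end of the 24-month follow-up compared to the baseline level".
- Numbers: the abstract says "The final analysis will include 86 patients (43 per group"), while *Sample size {14}* gives the same figure as the minimum enrolment: "Considering the potential of 20% of patients missing the obligatory follow-up procedures, we plan to include at least 86 patients".

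Nowhere does the protocol say that an excluded patient stays in the analysis set, that data already collected are used, or that the patient may return for the month-24 assessment.

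**The concern.** Three of the four visits at which the rule can act come before the primary time point. A patient who cannot be found around month 3, 6 or 12 is excluded before the 24-month ODI falls due. A patient located three weeks after the month-24 date is excluded although the outcome could be taken that day.

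The trigger is post-randomisation behaviour in an open-label surgical trial. Being hard to reach may be related to arm or outcome: a patient may have been reoperated elsewhere, be dissatisfied, or be well and see no reason to return. If such patients leave the analysis, the randomised comparison is no longer protected. If they stay in but are not followed, imputation replaces values that could have been observed. The rule would also end collection of complications and repeat surgery, which Table 2 schedules at every visit and which feed the planned Kaplan–Meier comparison.

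**Working it through.** **1. The passages side by side.** 

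- *Literal reading:* excluded from the study means out of the analysis. Intention to treat keeps every randomised patient in, so the two conflict. Imputation has little left to act on if patients with missing outcomes are removed. If enrolment stops at 86, an analysis of 86 is impossible once anyone is excluded.
- *Lenient reading:* follow-up stops, but the patient stays in the analysis and the outcome is imputed. The conflict with {20a}, {20c} and the abstract disappears. The month-24 ODI is still not sought from a patient lost earlier, nor accepted from one found late.

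The loss of obtainable primary outcomes is therefore common to both readings. The conflict with the analysis plan arises only on the first.

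**2. The plan's own numbers.** With SD 20, margin 12 and 80% power, 2 × (1.645 + 0.842)² × 20² / 12² = 34.4, so 35 per arm and 70 in total. This matches the stated 70 but uses a one-sided 5% level; a one-sided 2.5% level gives 44 per arm, 88 in total. That mismatch is a separate matter and nothing below depends on it. For the loss allowance, 70 / 0.8 = 87.5 and 70 × 1.2 = 84; the stated 86 lies between. Going from 86 to 70 is a loss of 16/86 = 18.6%.

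**3. Illustration of the data loss.** Let q be the probability that a patient is not found within 2 weeks at a given visit, after letters and a call. The documents give no value, so q is an assumption. Take 86 patients and four visits.

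- Rule in force, non-contact independent across visits: 86 × (1 − q)⁴ have a month-24 ODI.
- No rule, a missed contact costs only that visit: 86 × (1 − q).
- Full persistence (the same patients are unreachable at every visit): 86 × (1 − q) with or without the rule.

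| q (assumed) | Lost by month 24, 1 − (1 − q)⁴ | ODI at 24 months with rule, independent | ODI at 24 months without rule | Extra loss from rule: full persistence to independence |
|---|---|---|---|---|
| 2% | 7.8% | 79.3 | 84.3 | 0 to 5 |
| 5% | 18.5% | 70.0 | 81.7 | 0 to 12 |
| 10% | 34.4% | 56.4 | 77.4 | 0 to 21 |

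Under independence, q = 1 − 0.8^(1/4) = 5.4% per visit would by itself use up the whole 20% allowance. The column without the rule counts anyone not found within 2 weeks at month 24 as missing; accepting late values would reduce that loss.

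**The case against.** The strongest defence is that the sentence sits under retention, not analysis. Who is analysed is governed by {20a}, missing outcomes by {20c}, and the abstract's 86 equals the enrolment target. Read together, these allow the lenient meaning. This stands in part: a reader might infer that the protocol definitely deletes these patients from the primary analysis, and the text does not establish that. It does not rescue the rule, because the lenient meaning is not stated and still forgoes month-24 data.

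Four further limits also stand:

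- A reader might infer that one missed visit is enough for exclusion. It is not. The patient must leave the letters unanswered and still not be found after a phone call. Someone who misses a visit but replies is not covered, so a missed-visit rate is the wrong input and the non-contact rate should be lower.
- The larger losses depend on independence across visits. Some persistence is plausible, and full persistence brings the extra loss to zero.
- At q = 5% even the independent case leaves 70, the number the plan says it needs. Only the higher assumed rate falls below it. To say that the trial is already short of power would rest on the significance-level question in {14}, not on this rule.
- A reader might infer bias in a particular direction. The plausible mechanisms point opposite ways and the document gives nothing to weigh them.

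**Conclusion.** The concern holds in limited form. The rule as written conflicts with the stated analysis principle, the imputation plan and the number to be analysed, unless a meaning is supplied that the protocol does not give. On either meaning it gives up 24-month ODI values that could have been obtained.

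The extra loss attributable to the rule is between 0 and about 12 of 86 patients at an assumed 5% non-contact per visit, 0 to about 5 at 2%, and 0 to about 21 at 10%. Zero corresponds to full persistence and the upper figure to independence. The textual conflict does not depend on any of these rates. Bias in the arm comparison is possible, but neither its direction nor its size can be derived from the document.

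**What to change.** Replace the exclusion sentence in {18b} with:

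> A patient who cannot be reached for a visit is recorded as missing for that visit only, remains in the ITT set, and is contacted again for all later visits including month 24. A 24-month ODI obtained late is recorded with its date and used. Outcomes still missing are multiply imputed.

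Add that follow-up ends only on withdrawal as described in *Criteria for discontinuing or modifying allocated interventions {11b}*, and that data collected up to then stay in the analysis. That section covers withdrawal by the investigator as well as by the patient, so a rule that only withdrawn consent ends follow-up would create a new contradiction.

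Remote completion of the ODI could be a useful fallback, but *Participant timeline {13}* and *Plans for assessment and collection of outcomes {18a}* place questionnaires at personal visits to the operating centre. If remote completion is allowed, amend both sections to match and record the mode of collection.

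The cost is a short amendment, a few more contact attempts per unreachable patient, and some ODI values collected late or by a different mode.
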